### Intervention details

Once children are enrolled, schools will be randomised to receive either the SFI or treatment as usual. These treatment conditions are described as below.

#### Smoke free intervention

SFI is based on behaviour change techniques identified in the literature,^19^ and has been developed by a technical working group including schoolteachers, representatives of civil society organisations, public health practitioners, educational experts and behavioural scientists from Bangladesh and the UK. Once agreement was reached on the key messages, a range of educational materials, both in Bangla and English, were developed addressing different learning styles. The training materials for schoolteachers have been pre-piloted and revised according to the suggestions made by a user group and the technical working group. A manual has also been prepared to help schoolteachers in delivering SFI. It is envisaged that at least two year-5 teachers (one class teacher and one support teacher) will be trained in each school.

All participating children in the intervention arm will receive the SFI delivered by their teachers. Teachers will receive prior training in delivering the intervention. The intervention will consist of:
Two 45 min sessions delivered over 2 days by schoolteachers. The duration of these sessions is consistent with regular school lessons. Each session consists of a range of educational activities including classroom presentations, quiz, interactive games, storytelling and role-play—vicarious learning techniques are utilised in many of these activities. The presentation, quiz and games are designed to increase pupils’ knowledge about SHS and related harms, and motivate them to follow three easy steps to make their homes smoke-free. The storybook and role-play focuses on enhancing children's negotiation skills, building their confidence within the Bangladeshi cultural context. While the storybook depicts the challenges of negotiating with elders, the role-play has hypothetical scenarios where children had an opportunity to practise and demonstrate how and when they can discuss and negotiate with elders to persuade them not to smoke inside homes.A set of four refresher sessions (15 min each) to reinforce key messages delivered in the initial sessions, to be delivered once a week over 6–7 weeks after the two initial sessions. During each session, the teacher reminds children of the key points of the main session by asking questions (5–7 min), and then encouraging students to share their experiences of whether they could initiate discussion at home, what challenges they faced, what is their plan to do next and what would be the best way to convince the elders (8–10 min). The length of these sessions is consistent with the duration of the school assembly.Children are given a promise form that contains pictorial and written messages on the hazards of SHS, a pictorial step-guide for families on how to make their homes smoke-free and a tear-off slip to make a commitment to impose smoking restrictions at home. Children take promise forms to their parents, show them the messages and negotiate with them to ‘sign-up’ to the SFI ‘promise’ form. One of the implications is that even if parents are non-smokers, they will not allow other smokers (residents and visitors) to smoke inside homes. In addition to delivering the intervention, teachers will also be trained to support children in this process.

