## Methods and analysis

This is a two-arm pilot cluster randomised controlled trial (RCT) of SFI with an embedded preliminary health economic analysis and a qualitative evaluation. This is a 2-year study. We will recruit participants (schools and children) and start baseline assessments in the first 3 months. Between months 3 and 6, we will complete all baseline assessments, randomise schools and start delivering the intervention. We expect respective schools to have delivered the intervention by month 9, which means that all follow-ups will be completed between months 18 and 21. We will complete the analysis in the last 3 months and submit our final report at the end of 2 years.

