### Primary outcome

We will assess children's exposure to SHS by measuring their salivary cotinine levels. Salivary cotinine concentration, a sensitive biochemical marker, is strongly associated with the exposure to SHS at home. It has a half-life of 20 h. It is a widely recognised method for detecting both active and passive smoking and has been used in several surveys and studies. It involves keeping a sterile swab in the mouth for a few seconds, allowing it to absorb saliva and then transferring it to a sterile plastic container. The samples are subsequently analysed and a gas-liquid chromatography technique can detect cotinine levels as low as 0.1 ng/mL.

Once children are enrolled in the study, saliva samples will be obtained from all participating children at baseline and also at 2-month post-intervention. Samples can be stored for a period of 2 weeks before being transported to a specialist laboratory (ABS Labs) in the UK for these to be analysed using a gas-liquid chromatography technique. Samples will be sent in two batches at baseline and two at the first follow-up. Samples will not contain any participant identifiable information and will only have the trial enrolment number. Their reports will be sent back to the central research office in Dhaka where these will be entered in the database.

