#### Fidelity index

The research team will use a fidelity index, mapped onto the behaviour change techniques that underpin SFI, to assess intervention adherence. This will be in the form of a checklist, which will be used to monitor the delivery of SFI sessions. One of the members of the research team will attend all SFI sessions and using the above checklist will score fidelity to SFI.

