### Data collection

Prior to randomisation, a baseline assessment will include a classroom-administered questionnaire (including EQ-5DY, health service use and smoking behaviour) to be completed by participating children, APQ and school absenteeism form to be completed by school teachers, lung function assessment and saliva sample collection by the research team for each child (table 1). Each child will also receive a respiratory symptoms diary with instructions on how to use it. Follow-up assessment will take place at 2, 6 and 12 months post-allocation involving only those children whose cotinine levels were indicative of SHS exposure at baseline. All assessments carried out at baseline will be repeated at the follow-up assessment except cotinine levels which will only be assessed at month 2.

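### The only follow-up cotinine sample is dated by two conflicting clocks, and the length of delivery is stated inconsistently, so schools could be sampled before delivery has ended

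*Protocol article*

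**What the plan says.** **Delivery.** The Smoke free intervention section describes "Two 45 min sessions delivered over 2 days by schoolteachers", then "A set of four refresher sessions (15 min each) to reinforce key messages delivered in the initial sessions", which are "to be delivered once a week over 6–7 weeks after the two initial sessions". Table 1 marks the intervention in the Month 1 column only.

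**Cotinine.** The Primary outcome section says "saliva samples will be obtained from all participating children at baseline and also at 2-month post-intervention". The Data collection section says "Follow-up assessment will take place at 2, 6 and 12 months post-allocation", and adds that cotinine is repeated at month 2 only. Table 1 puts the month-2 sample under its post-allocation heading.

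**Timeline.** The opening of Methods and analysis places the completion of baseline, the randomisation of schools and the start of delivery between study months 3 and 6. It expects delivery to be finished by month 9, and from that concludes that "all follow-ups will be completed between months 18 and 21".

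**Pairing.** The Cluster randomisation and allocation section pairs each intervention school with a control school for follow-up.

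**The concern.** The pilot has a single post-baseline reading of its primary outcome, and two of its listed outputs, the effect size for cotinine and the ICC, rest on that reading. The article gives cotinine a half-life of 20 h, so a sample reflects exposure only shortly before it is taken. Where the sample falls relative to the sessions therefore decides what is measured, and no later cotinine sample could correct a badly timed one.

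The two clocks differ by the lag from allocation to the first session plus the length of delivery. The article does not state the first, and it states the second inconsistently. On the post-allocation clock the sample could precede the last refresher in some schools and follow it by weeks in others. The effect estimate would then mix partly and fully delivered intervention, and differences in timing between schools would enter the between-school variance behind the ICC.

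The post-intervention clock has a gap of its own. Control schools receive no intervention during the trial, so that clock gives them no date unless they borrow one from their paired school.

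**Working it through.** **Step 1. The refresher schedule.** Inputs: 4 sessions, one a week, 6–7 weeks (Smoke free intervention section).

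- Four sessions at one a week: 4 × 1 = 4 weeks, not 6–7.
- One a week for 6–7 weeks: 6 or 7 sessions, not 4.
- Four sessions spread over the stated span: 6/4 = 1.5 to 7/3 = 2.3 weeks apart, depending on how the ends are counted.

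The stated span is not reproduced on a literal reading. It is reproduced only if weekly means at most one a week with gap weeks, which the text does not say. A 6–7 week course also does not fit the single Month 1 mark in Table 1.

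**Step 2. When delivery ends.** Assume that delivery starts on the day of allocation (the article does not say so) and that it lasts 2 days for the initial sessions plus the refresher weeks: end day = 2 + 7 × weeks. Month 2 after allocation is 2 × 365.25/12 = 60.9 days. The slack is month 2 minus the end day. It is also the longest lag from allocation to first session that still leaves the sample after delivery.

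| Refresher span | End of delivery | Slack to day 60.9 | Slack if month 2 is day 56 |
|---|---|---|---|
| 4 weeks | day 30 | 30.9 days | 26 days |
| 6 weeks | day 44 | 16.9 days | 12 days |
| 7 weeks | day 51 | 9.9 days | 5 days |

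The end days run to the close of the last week. If the last session falls earlier in that week, the slack grows by a few days.

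**Step 3. What the timeline allows.** A school allocated at month 6 and finishing delivery at month 9 is within the stated plan, with 9 − 6 = 3 months between the two. On the post-allocation clock its sample falls at month 6 + 2 = 8, before month 9.

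**Step 4. Which clock the timeline fits.**

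- 12 months after allocation in months 3–6: months 15–18.
- 12 months after delivery ending in months 6–9: months 18–21, as stated.

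So the timeline fits a clock started at the end of delivery, in line with the Primary outcome section and against the Data collection section and Table 1.

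**The case against.** The strongest reply is that the refresher wording alone does no harm to the primary outcome. This is correct. Even a 7-week course begun at allocation ends by about day 51, before about day 61. For the sample to fall inside delivery, the post-allocation clock must apply and the first session must come later than the slack in the table. The article states no such lag. It says that teachers are trained beforehand, but not whether training comes before or after allocation. It also says that outcomes are measured before and after the intervention, so sampling during delivery is plainly not intended. On the post-intervention clock, if that means after the last session, the sample follows delivery whatever the span.

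Nor is the timeline evidence decisive. Table 1 has a close-out column at Month 15, and allocation in months 3–6 plus 15 also gives months 18–21. However, that column holds no assessments, and the text derives its window from the end of delivery. The evidence supports an end-of-delivery clock but does not prove it.

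A delivery manual exists and may hold the timetable. That could account for missing detail, but not for two clocks in one article.

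A reader might also infer that fidelity has no fixed denominator. The article does not support that. The session count is stated, 2 + 4 = 6, which agrees with the six activities in the Abstract if an activity is a session. Fidelity is scored on a checklist of behaviour change techniques: "One of the members of the research team will attend all SFI sessions and using the above checklist will score fidelity to SFI". The span of the refreshers does not change that count.

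**Conclusion.** The point holds as a conflict over the timing of the primary outcome, made worse by an inconsistent length of delivery. The two clocks cannot both apply, and the refresher sentence does not agree with itself on a literal reading or with Table 1.

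On the post-allocation clock the margin before the sample falls inside delivery is about 31 days for a 4-week course but only about 10–17 days for a 6–7 week course (5–12 days if month 2 means day 56). The study timeline allows about three months from randomisation to the end of delivery, so the plan as written permits sampling before delivery is complete. These figures assume the 2-day initial block and whole refresher weeks. The three-month case takes allocation at month 6 and delivery ending at month 9, the latest dates given. How many schools would be affected cannot be worked out from the article.

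A reader might go further and conclude that the effect would be understated. The article does not fix a direction: an early sample could miss the last refreshers, but it could also catch an effect that later fades. This is a pilot that does not set out to test for a difference between arms, so the harm is to the parameters it hands on, not to a test result. It should be corrected, at moderate priority.

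**What to change.** 1. In the Smoke free intervention section, reconcile the number, frequency and span of the refresher sessions, and bring Table 1 into line. Which schedule is right is for the investigators; this review does not choose one.
2. Use one clock for the cotinine sample in the Primary outcome section, the Data collection section and Table 1. Tie it to the last scheduled session so that the sample cannot precede it.
3. Give each control school the same calendar date as its paired intervention school. The pairing already exists.
4. Record the date of every session and of the cotinine sample for each school, so that the interval can be reported alongside the effect size and ICC.

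The cost is protocol wording and a few dates per school, with no extra visits or samples. If the 2-month interval is kept and delivery is finished by month 9, the latest sample falls at month 9 + 2 = 11, well inside the two-year study.

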#### Treatment as usual

Schools in the control arm will receive the intervention at the completion of the trial.

### Outcomes assessment

Specific outcomes for this pilot trial include: (1) number of clusters (schools) and the size of each cluster (children) for the main trial; (2) recruitment and attrition rates for clusters and participants; (3) length of time required to reach participant recruitment saturation for each cluster; (4) descriptive data on characteristics of participating clusters and participants; (5) reasons for ineligibility of clusters and participants; (6) reasons for non-participation/non-consent of clusters and participants; (7) estimate of the effect size of the primary outcome in a definitive trial (salivary cotinine); (8) calculation of the ICC for the trial outcomes in order to inform the sample size required for the main trial; (9) estimate of contamination between clusters; (10) the costs associated with delivering SFI; (11) fidelity of the intervention and (12) the time and resources required in measuring all outcomes, including the response rate to obtaining saliva samples and the extent and type of missing data with reasons. We will assess and report on these outcomes as part of our data collection and analysis plan.

The outcomes for the definitive trial will also be measured before and after the intervention in each of the study's arms. We first describe these outcomes and then the process and schedule of assessing these (table 1).

**Table 1 BMJOPEN2015008749TB1:** Table and schedule of assessments within CLASS II trial

	Study period						
	Enrolment	Allocation	Postallocation				Close-out
Time points	Baseline—t_0_	0	Month 1—t_1_	Month 2—t_2_	Month 6—t_3_	Month 12—t_4_	Month 15—t_x_
*Enrolment*							
Eligibility screen	X						
Parental consent	X						
Children's consent	X						
Allocation		X					
*Interventions*							
Smoke-free intervention			fx1				
Controls			fx2				
*Assessments*							
Sociodemographic and medical history							
Personal details	X						
Household details	X						
Medical history	X						
Smoking-related behaviours							
Smoking restrictions	X			X	X	X	
Attitudes towards smoking	X			X	X	X	
Health service use	X			X	X	X	
Quality of life	X			X	X	X	
Exposure to SHS—salivary cotinine	X			X			
Lung health	X			X			
Respiratory symptoms diary			X	X	X	X	
Lung functions—spirometry	X			X	X	X	
Academic assessment							
Academic performance questionnaire	X			X	X	X	
School absenteeism report	X			X	X	X	

CLASS, Children Learning About Secondhand Smoke; SHS, secondhand smoke.

### Primary outcome

We will assess children's exposure to SHS by measuring their salivary cotinine levels. Salivary cotinine concentration, a sensitive biochemical marker, is strongly associated with the exposure to SHS at home. It has a half-life of 20 h. It is a widely recognised method for detecting both active and passive smoking and has been used in several surveys and studies. It involves keeping a sterile swab in the mouth for a few seconds, allowing it to absorb saliva and then transferring it to a sterile plastic container. The samples are subsequently analysed and a gas-liquid chromatography technique can detect cotinine levels as low as 0.1 ng/mL.

Once children are enrolled in the study, saliva samples will be obtained from all participating children at baseline and also at 2-month post-intervention. Samples can be stored for a period of 2 weeks before being transported to a specialist laboratory (ABS Labs) in the UK for these to be analysed using a gas-liquid chromatography technique. Samples will be sent in two batches at baseline and two at the first follow-up. Samples will not contain any participant identifiable information and will only have the trial enrolment number. Their reports will be sent back to the central research office in Dhaka where these will be entered in the database.

### Secondary outcomes

These will include the below.

#### Frequency and severity of respiratory symptoms

Participating children will keep diaries and record respiratory symptoms on a nominal severity scale from 0 to 3 as used by Chauhan *et al*.^20^ For each item, ‘0’ representing the absence of a symptom, 1 representing mild, 2 representing moderate and 3 representing the greatest severity level. The upper respiratory tract symptoms will include having a runny nose or sneezing, blocked or stuffy nose, sore throat or hoarse voice, headaches or face aches, aches or pains elsewhere, and feeling chill, fever or shivers. The lower respiratory symptoms will include cough on waking, wheeze on waking, cough during the day, wheeze during the day, shortness of breath during the day, night cough and wheeze or shortness of breath during the night. Scores will be recorded daily and added up to give daily upper and lower respiratory-tract scores, respectively.

Three hundred and sixty diaries to record respiratory symptoms will be printed and given to all participating children. These diaries will have three sections. Section 1 will record symptoms from the day intervention is delivered until the end of month 2; section 2 from the start of month 3 until the end of month 6; and section 3 from the start of month 7 until the end of month 12. At each follow-up, one section will be taken out of the diary by the researchers and data will be entered in the database. All children will provide data on section 1. Only those children whose cotinine levels are indicative of passive smoking at baseline will provide data on sections 2 and 3. Children will be told whether to stop or keep collecting information in their diaries in a letter.

#### Lung functions

We will measure lung functions on all participating children at baseline and on children with positive salivary cotinine at months 2, 6 and 12. For this, we will use a spirometer as per British Thoracic Society guidelines.^21^ This will involve measuring forced vital capacity, forced expiratory volume in the first second (FEV1) and peak expiratory flow using a handheld Micro1 spirometer. We will first record the height of all participating children at baseline. We will enter details of the patient's sex, ethnic group, age and height into the spirometer. We will then ask each child to blow into a disposable mouthpiece attached to the spirometer at least three times as per guidelines. The best of the three readings will be taken. The spirometer will also calculate the percentage of the predicted normal values (using Asian reference values) as they have the reference data already programmed into them. The spirometer will print out a lung function test report for each participant, which will be attached to the participant baseline and follow-up questionnaire, respectively. Spirometers will be cleaned according to the manufacturer's guidelines and their accuracy checked regularly.

#### Smoking-related behaviours

We will ask the children to self-report levels of smoking restrictions and social visibility of smoking at home through a questionnaire. We will assess smoking restrictions using the following questions: (1) ‘Where do people smoke in your house who live with you? (Anywhere inside the house, in some rooms, only in one room, or only outside the house)’; (2) ‘Where do smokers who visit your house smoke? (Anywhere inside the house, in some rooms, only in one room, or only outside the house)’. We define ‘open space outside house’ as those spaces, which are still within the house premises but not covered by a ceiling, such as the veranda, balcony, yard, garden, lawn, patio and open roof. Social visibility will be assessed by the following questions; (1) ‘Do people who live with you smoke in front of children?’ (2) ‘Are people who visit your house allowed to smoke in front of children?’ For each outcome, the response categories across the two questions will be combined to form a composite variable (index) for analysis purposes.

Using the same questionnaire, we will also assess children's self-reported attitude towards smoking and intention to start smoking. We will use a five-point smoking uptake scale^22^ to categorise children as non-susceptible non-smokers, susceptible non-smokers, early experimenters, advanced experimenters and established smokers.

The above assessments will be carried out both at baseline and at all follow-up time points.

#### Health service use

We will use a health service utilisation questionnaire previously used in the Muslim communities learning about secondhand smoke (MCLASS) trial,^23^ to collect the number and type of contacts with doctors/nurses, hospital admissions, pharmacy visits and antibiotic prescriptions. This information will be part of the baseline questionnaire but will also be assessed at all follow-up time points.

